### Primary objective: to determine baseline prevalence and incidence of AF on a variety of screening strategies

Proportions and rates will be used as the measures of prevalence and incidence.

The independent t-test and ANOVA with random effects (as appropriate) will be used to examine the detection rate differences between the intervention and control screening strategies. Should the data be strongly non-normal a non-parametric equivalent will be used.

### Secondary objectives

a) to assess patient acceptability and impact on QoL of different screening strategies

The independent and related t-test and ANOVA will be used to examine the differences between the intervention screening strategies on the Spielberger and EuroQol EQ5D. Should the data be strongly non-normal a non-parametric equivalent will be used. Chi squared tests will be used on the screening tool.

b) to assess the value of echocardiography in risk stratification for thromboembolic disease in patients with AF

McNemar's test will be used to see whether there is any significant change in the doctor opinion on risk of CVA and treatment decision before and after echo screening.

c) to evaluate the most cost effective method of test interpretation

The cost effectiveness will be covered in the economic section. However, the use of sensitivity, specificity, Cohen's κ and conditional logistic modelling will allow for comparison of the various methods for detecting AF between the GPs, nurses and consultants.

d) to evaluate the most cost effective method of screening

This will be covered in the economic analysis section.

Multivariate and logistic modelling analyses will be undertaken in order to determine which markers might be the best predictors of the presence of AF. This will act as confirmatory analysis for the risk factors used in the screening strategy to define a high risk patient.

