Patient acceptability and quality of life for different screening strategies were established using EuroQol (EQ-5D) combined together with the Speilberger 6-item Anxiety Questionnaire. EQ-5D allowed the measurement of broad aspects of quality of life. The shortened Speilberger anxiety questionnaire also has proven validity and is more specific to anxiety than is the SF-12 [17]. An adapted version of the screening-specific tool used in the Colorectal Screening Programme [18] was used to assess the acceptability of the screening process.

A random sample of 750 patients (375 screened patients and 375 opportunistically screened patients) were sent postal versions of the psychological instruments (EQ-5D and Spielberger) on entry to the study (i.e. before the intervention group has received their invitation to attend for screening). One reminder was sent a month later to non-responders. The same questionnaires were sent to the same groups plus those patients who had screened postive at the end of the screening period, approximately 17 months later. This allowed a non-randomised comparison between the effects on quality of life and anxiety in screen positive and screen negative patients.

In addition, all patients who were screened were asked to complete the acceptability and Spielberger questionnaire immediately after screening. The patient acceptability questionnaire was also administered to all patients who proceeded for echo.

The value of clinical assessment and echocardiography in risk stratification were determined in patients aged 65–74. This compared GP assessment based on the Birmingham guidelines for thromboprophylaxis in AF with any changes in recommendations for treatment once echocardiography results were available to the GP.

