### Spielberger

The shortened (6-item) version of the Spielberger state anxiety questionnaire has been validated and used in populations different from that under consideration in SAFE, namely it tends to have been used in young and mostly female populations [17,21,22]. The variance obtained from these papers appears to be approximately 144 for Marteau [17] but higher for the Ubhi [22] paper. However, the women in the latter paper were being informed of major illness outcomes (either benign or malignant breast cancer). A full Spielberger on people undergoing physiological tests also gave a variance of the order of 144 [23]. The full version of the Spielberger state anxiety when used with an elderly population also seems to give a variance that is not too far from the previously mentioned papers being 188.8 [23]. Taking this latter value as being the nearest to our population we can detect a 4 point difference in the mean values obtained with 249 patients in each arm.

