### Statistical analysis

Intention to treat analysis will be used.

Any previously known Atrial Fibrillation cases will be subtracted from the totals obtained at the end of the study to ensure there is no double counting in the incidence figures.

Chi-squared, independent t-tests and log-linear models will be used to describe demographic data. If there are differences between the groups this may need to be adjusted for in later analyses.

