#### Screening clinics

All patients in the systematic screening arm and those found to have an irregular pulse in the opportunistic screening arm of the study were invited to attend an ECG screening clinic. At the clinic the practice nurse explained the aims of the study and answered any questions about the study. Written informed consent to participation in the study was obtained from the patient. The nurse then recorded baseline information on age, sex, present smoking and alcohol status and past medical history, including previous diagnosis of AF, and any treatment the patient may be receiving for AF. Radial pulse rate, and whether regular or irregular, was noted. A 12 lead ECG, the gold standard by which other traces were compared, was then recorded using the Biolog machine, which was also able to produce a trace corresponding to the single lead thoracic placement and a rhythm strip of lead II. Finally, the patient was asked to complete an acceptability questionnaire.

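### The anxiety and EQ-5D comparison between strategies leaves out baseline scores that were collected (a loss of precision, not a bias), and questionnaires completed at the clinic cannot support a randomised comparison of strategies

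*Protocol article*

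**What the plan says.** All references are to the protocol article.

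- **Planned test.** Statistical analysis, Secondary objectives, item a): "The independent and related t-test and ANOVA will be used to examine the differences between the intervention screening strategies", with Spielberger and EQ-5D as the outcomes. A non-parametric equivalent is the fallback for strongly non-normal data, and chi-squared tests are named for the screening (acceptability) tool. The groups for the chi-squared tests are not named.
- **Adjustment.** The opening of Statistical analysis, after describing tests on demographic data, adds: "If there are differences between the groups this may need to be adjusted for in later analyses". Baseline questionnaire scores are not mentioned.
- **Postal data.** Methods, text after Figure 1: "A random sample of 750 patients (375 screened patients and 375 opportunistically screened patients) were sent postal versions of the psychological instruments". This was done on entry, before any invitation, with a second mailing about 17 months later to the same groups plus patients who had screened positive.
- **Data after screening.** Same section: "all patients who were screened were asked to complete the acceptability and Spielberger questionnaire immediately after screening". EQ-5D is not in that list.
- **Who reaches the clinic.** Screening clinics: everyone in the systematic arm was invited, and "those found to have an irregular pulse in the opportunistic screening arm of the study were invited to attend an ECG screening clinic". That section closes the clinic visit with the acceptability questionnaire and does not mention Spielberger.
- **Sizing.** Spielberger section, with variance 188.8: "we can detect a 4 point difference in the mean values obtained with 249 patients in each arm".

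**The concern.** There are two separate issues, with different consequences.

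**Precision in the postal sample.** An independent t-test on the 17-month score ignores the entry score. A related t-test assesses change within one group and does not itself compare strategies. ANOVA is named without a covariate. The adjustment sentence is triggered by observed differences and follows a statement about demographics. So no baseline-adjusted comparison of strategies is fixed in advance, although the data for one exist. What is lost is precision, in a sample that depends on two postal returns from people aged 65 and over.

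**Comparability of the clinic data.** Systematic attenders come to the clinic whatever their pulse. Opportunistic attenders come only because someone has already found their pulse irregular. If acceptability or immediate anxiety is set side by side by strategy, the contrast mixes the effect of the strategy with the effect of having had an abnormal finding. The article calls the screen-positive versus screen-negative comparison non-randomised, but gives no such caution here.

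**Working it through.** **Inputs from the document.** Spielberger variance 188.8, difference 4, 249 per arm (Spielberger section); 90% power and 5% significance (Sample size and power calculations); 375 per arm mailed (Methods). **Assumed, not in the document:** the correlation r between entry and 17-month scores, the anxiety difference d between irregular-pulse and other patients, and the share q of systematic attenders with an irregular pulse.

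**Step 1: reproduce the stated figure.** For an unadjusted two-sample comparison, two-sided 5%, 90% power:

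n per arm = 2 × variance × 10.507 / difference² = 2 × 188.8 × 10.507 / 16 = 248.

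The exact t calculation gives 249, as stated. The EQ-5D figures reproduce in the same way: VAS 214 (stated 213), utility 139 (139), the other index 248 (247). The plan was therefore sized without baseline adjustment, and correctly so on its own terms. Reaching 249 of 375 needs a 249/375 = 66.4% response. With all 375 responding, unadjusted Spielberger power is 97.9%.

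**Step 2: add the baseline score.** ANCOVA multiplies the variance by (1 − r²). A change-score analysis multiplies it by 2(1 − r).

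| assumed r | variance cut, ANCOVA | n per arm, ANCOVA | power at 249, ANCOVA | difference detectable at 249, 4 × √(1 − r²) | n per arm, change score |
|---|---|---|---|---|---|
| 0.4 | 16% | 209 | 94.3% | 3.67 | 298 |
| 0.5 | 25% | 186 | 96.3% | 3.46 | 248 |
| 0.6 | 36% | 159 | 98.2% | 3.20 | 199 |

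Over a wider range, r = 0.3 gives 226 per arm by ANCOVA and 348 by change score; r = 0.7 gives 127 and 149. A change-score comparison is less precise than ignoring baseline whenever r is below 0.5. ANCOVA never has that drawback at these sample sizes.

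**Step 3: missing baseline forms.** If a share m of follow-up responders returned no entry form and is dropped, the variance of the comparison scales as (1 − r²)/(1 − m). The gain is gone once m reaches r², which is 16% at r = 0.4 and 36% at r = 0.6. These responders therefore have to be kept in the model.

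**Step 4: clinic selection.** Suppose the strategies have no effect. If all opportunistic clinic patients have an irregular pulse, their mean is raised by d, and the systematic mean by q × d. The difference produced by selection alone is d(1 − q). With d = 4 and q of 5% to 20%, it is 4 × 0.95 = 3.8 down to 4 × 0.80 = 3.2 points. With d = 2 it is 1.9 to 1.6. The result is nearly proportional to the assumed d, so it shows the mechanism and does not estimate the bias.

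**The case against.** The strongest reply on precision is that nothing in the postal analysis is wrong. Patients in intervention practices were randomised individually, the unadjusted comparison is valid, the sizes reproduce, and with good response the power is ample. A condensed article often leaves covariates to a fuller plan; it also names ANOVA and leaves adjustment open. This stands as far as validity goes. It does not remove the point that the article names its tests for this objective and that a better one is available from data already collected.

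A second reply is that ANCOVA is not free if entry forms are missing. That stands, and Step 3 shows when it matters; simple handling of missing baselines answers it.

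On the clinic data, the reply is that the analysis section never says outright that clinic Spielberger scores are tested between strategies. It pairs Spielberger with EQ-5D, which is the postal set. The Methods wording on who completed forms after screening could also include opportunistic patients whose pulse was taken and found regular. Both observations stand. For acceptability the selection is explicit, because that form is placed at the clinic; for Spielberger it is conditional.

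A reader might infer that the unadjusted t-tests bias the anxiety and EQ-5D results, or that the clinic selection contaminates EQ-5D. The document supports neither. The postal sample was drawn before invitation, and EQ-5D was collected only by post. A reader might also think that restricting the clinic comparison to irregular-pulse patients in both arms would repair it. It would not: these are still subsets formed after randomisation, and opportunistic patients were found irregular before the visit whereas systematic patients have their pulse recorded at it, so prior knowledge stays confounded with strategy.

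**Conclusion.** The point holds in two limited parts.

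1. **Precision only.** The named tests leave out a baseline score that is available in the randomised 750. The gain forgone is a 16% to 36% reduction in residual variance if r lies between 0.4 and 0.6. This r is an assumption, and the gain shrinks to 9% at r = 0.3. The stated sample sizes are not in error, and the study is not shown to be underpowered.
2. **Comparability.** Acceptability, and Spielberger if completed at the clinic, comes from differently selected groups in the two arms. Any comparison of these data between strategies is non-randomised. Its direction and size cannot be established from the document.

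Both concern a secondary objective, and both can be corrected without new data.

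**What to change.** - **Postal outcomes.** Compare strategies by ANCOVA of the 17-month Spielberger and EQ-5D scores on arm, baseline score and practice. Use the randomised 750 only, leaving out the screen-positive patients added at follow-up. Keep follow-up responders who lack an entry form by simple imputation of the baseline score or a missing indicator. Do not use the related t-test as evidence of a difference between strategies.
- **Clinic outcomes.** State who completed Spielberger after screening and where. Label any comparison of clinic-completed acceptability or Spielberger between strategies as non-randomised, and report it descriptively by arm without a test. Do not present an irregular-pulse subset as a corrected comparison.

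The cost is analysis wording and, since the Discussion says a draft report has already been submitted, possibly a re-run. No new data are needed. What is given up is a significance test on the clinic data, which could not have been interpreted as an effect of strategy.

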#### The value of echocardiography

The main treatment options to reduce risk of stroke in patients' with AF are currently warfarin or aspirin. Aspirin is much less effective than warfarin – it achieves a barely significant 21% reduction in stroke risk [9]. However, it is safer to use, since it confers a lower risk of serious haemorrhage. Therefore, in practice, the clinical decision as to which treatment to use depends upon the balance of risks and benefits for the individual patient. Thromboembolic risk is currently determined primarily on clinical criteria. Data from the SPAF study [12] suggested that echocardiography (Echo) may inform on risk stratification, assisting in therapeutic decision making. The role of routine Echo for patients with AF identified in the community remains to be proven. Data also needs to be quantified regarding the cost effectiveness of Echo versus clinical impression alone. Studies have suggested that the clinical utility in people aged over 74 is poor [13,14]. Therefore this study focused on patients aged 65–74. Once somebody has been identified as having AF, should they also receive an echocardiogram to assess their risk of stroke, or is clinical assessment of risk adequate?

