All 12 lead ECGs were sent to two cardiologists for reporting ([name]). Where there was disagreement over the diagnosis a third cardiologist was used to decide. The cardiologists were asked to state whether the ECG showed AF or not, and to state whether there were any other significant abnormalities. Patients were informed of the result within two weeks. Patients with normal ECGs were informed of this, patients with any abnormality were asked to make an appointment with their GP. At the GP appointment patients with AF aged 65 – 74 were offered echocardiography. GPs were asked to make a clinical decision as to thromboprophylaxis both before and after the echocardiogram. Patients with other ECG abnormalities were managed as clinically indicated.

At the end of the screening process, GPs and Practice Nurses from both intervention practices (who had received education on ECG interpretation) and control practices (who had received no education) were sent ECGs to interpret for the presence or absence of AF. All ECGs recorded within the study were printed off as either 12 lead, single lead thoracic placement or limb lead recordings. Allocation to ECG type was random and resulted in three equal ECG groups. In order for each interpreter to read all three types of ECG, batches of ECGs were collated with the same numbers of each type of ECG. Allocation to a batch was also random. In total, there were 25 batches of ECGs to match the number of practices in each arm. The GP and Practice Nurse from the same practice read the same batch of ECGs and each batch was read by one control practice and one intervention practice. Therefore each ECG was read by two GPs and two Practice Nurses. All ECGs were anonymised, and practices did not receive any ECGs from their own practice. The interpreters were given a sheet to fill in to indicate for each ECG the presence or absence of AF. All ECGs (as 12 lead) were also analysed by the specific software package accompanying the electronic ECG and results recorded.

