### Sample size and power calculations

The assumptions for the power calculations were that patients aged 65 and over represent 17% of the total population; that 40% of study population will be in the high risk group.

Also assuming that:

1. Minimum worthwhile change in detection rate was 1% for targeted screening versus routine practice. It is estimated that this change would equate to £10,000 per life year gained. This is based on the following assumptions:

a) 60% of new cases of identified AF would be suitable candidates for warfarin

b) Annual risk of stroke in this population was 5%, reduced by 60% to 2% if treated

c) Costs: £25 to screen a patient; £100 to treat with warfarin pa; £6,000 NHS costs to treat a stroke

2. 50% of patients with AF will be already known to their general practitioner (estimates range from 30% [19] to 76% [20])

3. Community prevalence of AF in this population was 6% [2]

See figure 1. It was assumed that the baseline prevalence of AF known to the practice (A1) would be 3% (i.e. half of real prevalence of 6%) and that the prevalence of known AF in the control practices would remain constant over the screening period. Thus, the change in the prevalence of known AF in the control practices between baseline to follow up (C2-C1) should be approximately 0%. The change in the GP educated arm (B2-A1) should be marginally higher and is assumed to be between 0 and 1%. The change in the systematic screening arm should, on average, be between 0 and 3% and was assumed to be approximately 2% for the total screening arm (A3-A1) and in the high risk arm (A2-A1) was approximately 3%.

All sample size calculations were for 90% power and 5% significance levels unless otherwise stated.

*a) To detect a 1% difference in detection rate between intervention (GP educated) and control practices (B2-A1) vs (C2-C1). *This requires 1,236 patients. However, since this is a difference based at the practice level of randomisation, it needed to be inflated by the design factor. Based on AF prevalence data from the EcHoES (Echocardiographic Heart of England Screening) Study [2], the between practice variance is 3.7 and the within practice variance is 246. This gave an intra-cluster correlation coefficient of 0.015. The most efficient design in this circumstance would be a cluster size of 200, which gives a design factor of 4. Therefore, 5,000 patients would be needed in 25 practices in both intervention (GP educated) and control groups.

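### McNemar's test, the only analysis named for the echocardiography objective, tests net shift in GP decisions, whereas the stated question is whether decisions changed at all

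*Protocol article*

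**What the plan says.** Under Statistical analysis, Secondary objectives, item b) is "to assess the value of echocardiography in risk stratification for thromboembolic disease in patients with AF". The one analysis named for it is: "McNemar's test will be used to see whether there is any significant change in the doctor opinion on risk of CVA and treatment decision", comparing the position before and after echo.

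The Methods (text following Figure 1) give the design. "At the GP appointment patients with AF aged 65 – 74 were offered echocardiography", and "GPs were asked to make a clinical decision as to thromboprophylaxis both before and after the echocardiogram". The data are thus paired within patient. The same section states what is compared: the GP's guideline-based assessment against "any changes in recommendations for treatment once echocardiography results were available to the GP".

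The Background section on the value of echocardiography gives the reason for asking. Echo "may inform on risk stratification, assisting in therapeutic decision making", and "the clinical decision as to which treatment to use depends upon the balance of risks and benefits for the individual patient".

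The article names no proportion of decisions changed, no agreement measure and no split by direction for this objective. Cohen's kappa appears only under item c), on ECG interpretation. No sample size is given for the echo comparison.

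**The concern.** The question is whether echo adds to clinical assessment in deciding about an individual patient. The direct measure is how often the decision differs once the echo result is known. McNemar's test uses only the imbalance between the two kinds of change. Patients moved up and patients moved down offset each other in the statistic, although each is a case in which echo altered the decision.

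At stake is how this secondary objective is read. A non-significant result, reported as no significant change, invites the conclusion that echo had little influence, even if many decisions were altered. A significant result could rest on a handful of one-way changes.

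**Working it through.** **Inputs.** The test, the question and the paired design come from the article as quoted. It gives no number of echo patients, no discordance rate and no direction of change, and it states no figure that could be reproduced. All counts below are assumptions.

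**Formulas.** Let *n* be the number of patients with a decision before and after echo, *b* the number changed in one direction and *c* the number changed in the other.

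- McNemar's statistic: (b − c)² / (b + c), on 1 degree of freedom. Exact version: b out of b + c against a probability of 0.5, two-sided.
- Null hypothesis: b and c are equal in expectation. It is not b + c = 0.
- Proportion changed: (b + c) / n.

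**Step 1: main illustration.** n = 60, b = c = 8.

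- Statistic: (8 − 8)² / 16 = 0, so p = 1.
- Proportion changed: 16/60 = 26.7%; Wilson 95% CI 17.1% to 39.0%.

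**Step 2: other assumed counts** (exact McNemar p; Clopper-Pearson 95% CI).

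| n | b | c | Changed (95% CI) | Exact p |
|---|---|---|---|---|
| 100 | 20 | 20 | 40% (30.3% to 50.3%) | 1.00 |
| 100 | 40 | 40 | 80% (70.8% to 87.3%) | 1.00 |
| 100 | 15 | 25 | 40% (30.3% to 50.3%) | 0.154 |
| 100 | 10 | 0 | 10% (4.9% to 17.6%) | 0.002 |
| 200 | 6 | 0 | 3% (1.1% to 6.4%) | 0.031 |

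The p-value does not order these cases by how often decisions changed. The 80% case has p = 1; the 3% case is significant at 5%.

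**Step 3: chance of a significant exact test at 5%, given the number of changed decisions.**

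| Changed decisions (b + c) | Split 50:50 | Split 60:40 | Split 70:30 |
|---|---|---|---|
| 10 | 2.2% | 4.8% | 14.9% |
| 20 | 4.1% | 12.7% | 41.6% |
| 40 | 3.9% | 21.2% | 70.3% |
| 80 | 3.3% | 36.9% | 94.1% |

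With balanced changes the chance stays below 5% however many decisions change, as it must, because balance is the null hypothesis. With a moderate imbalance of 60:40 and 40 changed decisions it is still only about 21%. It rises as the split becomes more one-sided.

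The intervals above treat patients as independent. Positive correlation within practices would widen them.

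**The case against.** The strongest reply is that McNemar's test is the standard test for paired binary decisions. It has the correct error rate for its own null hypothesis, and net shift is a legitimate quantity, for instance whether the share of patients given a particular treatment rises or falls. The test is computed from the paired table, so the two discordant counts, and with them the proportion changed, must be produced anyway. A journal article may leave tables and intervals to the full plan. If nearly all changes run one way, the test will find them once there are enough.

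All of that stands, and it limits the point. It does not remove it. The article does not merely omit reporting detail: it names the inferential criterion for this objective, and that criterion answers a different question from the one stated twice, namely whether there was *any* change.

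Three stronger readings are tempting but unsupported:

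- A reader might infer that the test fails because decisions fall into more than two categories. The article does not give the response format, and the Background names two main treatment options, which fits a binary decision at least as well.
- A reader might infer that a non-significant result would drive the service-provision conclusion. The Economic analysis section bases that on prevalence, the screening mechanism, the use of echo and anticoagulation monitoring, through modelling. It is not tied to this p-value.
- A reader might infer that echo-driven changes will balance. The Background makes movement in both directions plausible, but says nothing about its balance.

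**Conclusion.** The concern holds as a mismatch between question and test. McNemar's test is valid here for a net imbalance in either direction, but it does not measure how often echocardiography changed the GP's risk opinion or treatment decision. Under exact balance p = 1 at any rate of change (27% in the 60-patient illustration, 80% in the most extreme case). In the other direction, 3% changed one way is enough for p = 0.031.

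The practical size depends on the number of echo patients, the rate of change and its balance, none of which the article gives. If changes are mostly one-way, the test and the proportion will tell much the same story; the nearer to balance, the more misleading the test alone becomes.

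The point should be corrected but is confined to one secondary objective, in AF patients aged 65 to 74. The primary comparison of detection rates is unaffected. It would be wrong to read it as showing that the test is invalid, or that a non-significant result amounts to evidence of no change.

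**What to change.** Amend item b) of the Secondary objectives analysis as follows:

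- Main result: the proportion of patients whose decision changed in either direction after echocardiography, given for the risk opinion and for the treatment decision, each with a 95% CI that allows for clustering by practice.
- Supporting display: the full before/after table for each, with moves in each direction shown separately.
- Secondary test: McNemar's test, described as a test of net shift.

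The cost is a sentence or two in the analysis section. The paired decisions are already collected, so no new data, patients or design change are needed.
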